### Qualitative analysis

We will use the framework analysis approach proposed by [38] for analysis of qualitative data [38].

*Stage 1*: Transcription: All the audio recorded interviews will be transcribed verbatim by the master level psychologists with previous experience of transcription. Non-disclosure agreements would already be in place for these researchers. The qualitative researchers will randomly cross check the transcripts against the audio recording to ensure the accuracy and quality of the transcription.

*Stage 2*: Familiarization with the data: The qualitative researchers will read and re-read the transcripts and the reflective notes recorded by the interviewers to fully immerse themselves in the data set. They will also re-listen to the audio recording if needed. They will make their analytical notes, thoughts or impressions during the stage of familiarization.

*Stage 3*: Coding: The researcher, while reading the transcripts line by line, applies a label (a ‘code’) that would describe what they have interpreted in the passage as important. Coding will aim to classify all of the data so that it can be compared systematically with other transcripts. Two researchers will independently code at least 25% of the transcripts. Coding will be done manually with a paper and pen.

*Stage 4*: Developing a working analytical framework: After coding the 25% of transcripts, both researchers will meet to compare the labels they have applied and agree on a set of codes to apply to all subsequent transcripts. Codes will be grouped together into categories, which will be then clearly defined. The analytical framework will not be ‘final’ until the last transcript is coded.

*Stage 5*: Applying the analytical framework.

The working analytical framework will then be applied by indexing subsequent transcripts using the existing codes and categories.

*Stage 6*: Charting data into the framework matrix.

To manage and summarize the data, an excel spreadsheet/Nvivo will be used to generate a matrix, and the data will be ‘charted’ into the matrix. Charting involves summarizing the data by category from each transcript. Good charting will allow us to strike a balance between reducing the data on the one hand, and retaining the original meanings, and ‘feel’ of the participants’ words, on the other. The chart will include references to illustrative verbatim.

*Stage 7*: Interpreting the data.

Characteristics of and differences between the data will be identified, perhaps generating typologies, interrogating theoretical concepts (either prior concepts or ones emerging from the data) or mapping connections between categories to explore relationships and/or causality.

### Community Engagement and Involvement (CEI)

A Community Engagement and Involvement (CEI) group has been established to advise the research team during the development of research protocol. This group is comprised of five members and one CEI lead with lived experience. A detailed CEI plan was developed by the CEI lead in consultation with the CEI members. This CEI plan was discussed in a wider Community Engagement and Involvement Group and suggestions were incorporated. The CEI group has advised on the areas that should be assessed during the study, development of study material such as participant information leaflet, interview schedule, study adverts, and data collection questionnaires. The CEI group actively participated during the adaptation of the intervention. The research team will continue to engage with this group to develop robust recruitment and retention strategies, analysis of qualitative findings and development of dissemination material. The CEI group will also contribute to the community engagement activities.

### Communication plan

A comprehensive communication plan will be developed in collaboration with CEI group and other stakeholders by taking into consideration the culturally appropriate strategies to share the purpose and need of the project as well as the study findings. Partnership with the community has already been established as part of completed and ongoing suicide prevention work in Pakistan (CMAP MR/N006062/1; YCMAP MR/R022461/1; SEPAK GCRF Pump priming award; and SAHAR-M GCRFF006949). We will extend and further strengthen this network through engagement meetings with stakeholders, potential voluntary organizations, local health teams, primary care settings, GP practices, hospitals, and community centers in order to increase awareness and promote the study. We will use local mainstream and social media channels, press releases, posters, newsletters and information leaflets in English, Urdu, and other local languages, and clinical and local community settings to advertise the study to a wider audience. In addition, we will also organize community awareness workshops, seminars (through zoom or face to face) in catchment areas of the study with a particular focus on the low income and low literacy population. The results of the study will be written up for academic publications in peer reviewed, open access journals and in national and local newspaper articles in lay language. The results will also be further disseminated through presentations in international conferences, local and national TV and radio channels.

### Safety

As this study involves vulnerable people experiencing mental health difficulties, a safety protocol will be in place. The research team will receive regular ongoing supervision for managing distressed populations by an expert psychiatrist (NC), and an experienced clinical psychologist (TK). In case of any adverse event (i.e., suicide attempt or self-harm), an Adverse Event Form (AEF) will be completed and sent to the PI within 24 h of reporting of the event. The Project Management Committee is led by the senior consultant psychiatrist. This committee will meet on weekly basis to monitor the study progress and safety of the participants. Data management plan will be developed and adhered to. The identifying information will be kept in locked cabinet with access to authorized research team members. The audio-recordings of interviews will be saved in password protected computers.

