### Procedure

Ethics permission for the trial was sought from the National Bioethics Committee (NBC) of Pakistan (Ref: No.4-87/NBC-669/21/400). The trial is registered at clinicaltrials.gov (NCT05724394). Individuals who wish to participate in the study and are ready to sign informed consent will complete the consent process for screening (see Fig. 1 Trial Flow Chart). A trained researcher will assess the eligibility of the participants by using the study eligibility checklist. As part of eligibility assessment, the researchers will administer the BEDS-7 to screen for BED and the BITE to screen for BN. Eligible participants will be given a PIS and the purpose of the trial will be explained. All potential participants will have the opportunity to ask for more details about the study. Written consent will be obtained from all eligible participants who are willing to participate. Baseline assessments of consented participants will be conducted by the researchers trained in the Good Clinical Practice (GCP) who will administer study questionnaires. Assessments will be completed either face to face at a research office or recruiting health facility, or online over a telephone call or via Zoom link, depending on participant’s convenience. After completing baseline assessments, participants will be randomized into one of the two trial arms. Participants will be informed about the status of their allocated study arm within 1 week of randomization. Participants in the intervention arm will receive sessions of Ca-GBBB for a period of 16 weeks. Follow up assessment will be completed of all the participants regardless of their treatment arms at 16th week post-randomization. The assessments will take 45–60 min to complete.

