Chapter 5: Having your cake and eating it too	Facing the facts 1. Facts about effectiveness of weight control methods 2. It is right to worry Type of weight controller Tips to take a start 1. Planning how to start and adhere to the plan 2. How to cope with anxiety 3. Golden rules How to stop abusing laxatives, diuretics, medications 1. Coping with constipation 2. Coping with swelling
Chapter 6: Learning to feel good about your body	Learn to accept your body 1. How body image problems are caused and maintained 2. The role of media and social media 3. The perils of selective attention Getting to know your body Looking after your body Living with your body Other helpful strategies
Chapter 7: Being fatter may be better	Health risks in being overweight 1. Explained with examples Nothing is beautiful about dieting 1. Explained with examples Avoiding the lonely trap 1. Explained with examples 2. Importance of exercise Overcoming obstacles 1. How to deal with problems of eating disorder 2. Strategies to include in your lifestyle
Chapter 8: Relapse: Walking in circles—or not	Preventing slips 1. Plan your own relapse 2. Relapse Plan What to do if a slip occurs 1. Self-compassion 2. Self-kindness 3. Being aware of your mistakes Add pleasure to your day 1. Learning from slips 2. Chart activity
Chapter 9: Childhood Wounds	Sexual abuse 1. What is sexual abuse? 2. How do I know if I have been sexually abused? 3. Why is it wrong? Trying to make sense of it 1. Feelings of victims of sexual abuse 2. Explain with example 3. The right to be angry 4. What can you do with angry feelings? Grappling with guilt and self-blame 1. Identification of victims’ feelings of guilt and self-blame 2. Activity After-effects of abuse 1. Focusing on surviving Get a toehold on trust 1. Building trust on self and others Coming to terms 1. Accepting the past 2. Working out the need of counselling and therapy

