Participants’ convenience will be considered while deciding the time and venue of the sessions. Intervention will be delivered in weekly sessions over four months, and each session will last for 45–50 min. Special consideration will be given to the cultural adaptation of the content i.e. phrases of the manual while translating it into Urdu. Moreover, culturally relevant cases will be integrated, and a shared understanding will be aimed to address cultural aspects (gender roles and financial challenges etc.).

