#### Routine care

In Pakistan, standard routine care is provided by the local medical, psychiatric, and primary care services. Participants will receive a baseline evaluation along with routine care as determined by their treating physician. As part of the safety protocol, we will obtain the contact details of the participants’ GP. Details of any treatment received by all the participants will also be recorded in this study. Researchers delivering the interventions will have no contact and will not be involved with the participants in the routine care arm.

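### The adverse event definition is closed to suicide attempt and self-harm, so other harms trigger no form, and any counts shown by arm risk unequal detection unless both arms are asked in the same way

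*Protocol article*

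**What the plan says.** **Definition and reporting.** The Safety section states: "In case of any adverse event (i.e., suicide attempt or self-harm), an Adverse Event Form (AEF) will be completed". The form is to be "sent to the PI within 24 h of reporting of the event". The same section says that "a safety protocol will be in place", without giving its content, and says of the Project Management Committee: "This committee will meet on weekly basis to monitor the study progress and safety of the participants".

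**Contact by arm.** For the intervention arm, the Intervention section says: "Intervention will be delivered in weekly sessions over four months". For the comparator, the Routine care section says: "Researchers delivering the interventions will have no contact and will not be involved with the participants in the routine care arm". The common follow-up is in the Procedure section: "Follow up assessment will be completed of all the participants regardless of their treatment arms at 16th week post-randomization". Apart from notice of allocation within a week of randomization, the article describes no study contact with the routine care arm between baseline and week 16.

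**Other data from both arms.** Under Outcome assessment measures, the BITE, EDE-Q, Kessler scale, BDI and Beck suicide ideation scale (BSS) are given at baseline and at four months. Follow-up assessors are masked (Randomization and masking). The Routine care section adds that treatment received is recorded for every participant.

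**The concern.** *I.e.* means *that is*. It does not introduce examples. It equates an adverse event with two outcomes, and a researcher who follows the sentence literally has no reason to complete a form for anything else.

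The article itself makes other harms foreseeable. The Background reports mortality 5–7 times higher in people diagnosed during hospitalization. Table 1 includes the topic "How to stop abusing laxatives, diuretics, medications" (Chapter 5) and a chapter on sexual abuse (Chapter 9). The Safety section describes the participants as vulnerable.

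The second strand is opportunity. A participant who sees a therapist every week has many more occasions to mention a self-harm episode than one whose next described study contact is at week 16. If counts are tabulated by arm, an excess in the intervention arm could partly reflect better detection, and a low count in routine care could partly reflect events nobody heard about. The findings are meant to inform a fully powered trial, so a distorted harms table could mislead its planners even without a formal test.

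**Working it through.** **1. The definition, read against foreseeable harms.** No arithmetic is needed.

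| Harm | Triggers the form as written? | Recorded elsewhere in the article? |
|---|---|---|
| Suicide attempt, self-harm | Yes | BSS at week 16, but described as measuring suicidal thoughts |
| Death from another cause | No | No explicit record described |
| Hospital admission | No | Possibly, through the record of treatment received |
| Medical complication of purging or laxative use | No | Possibly, if treated |
| Marked worsening of eating symptoms or mood | No | BITE, EDE-Q, BDI and Kessler scale at week 16, both arms |
| Distress caused by a session | No | Feedback forms and interviews, intervention arm only |

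Nothing in the article links the third column to the Adverse Event Form.

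**2. Unequal detection: inputs.** The article gives no adverse event rate, so there is no figure to reproduce. The arm size is consistent: 80/2 = 40. The true risk *p*, taken as equal in both arms, and the probability *d* that an affected participant's event is logged are assumptions.

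**3. Formulas.**
- Expected participants with a logged event per arm = 40 × *p* × *d*.
- Apparent ratio under equal true risk = *d*(intervention) / *d*(routine care).
- Chance that an arm logs nobody = (1 − *p* × *d*)^40.
- Chance that the intervention arm logs more than routine care: from two independent binomials, each with n = 40 and probability *p* × *d*.

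**4. Results.**

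| *p* | *d* intervention | *d* routine care | Expected counts | Apparent ratio | Chance intervention arm logs more |
|---|---|---|---|---|---|
| 10% | 0.9 | 0.9 | 3.6 v 3.6 | 1.0 | 0.421 |
| 10% | 0.9 | 0.6 | 3.6 v 2.4 | 1.5 | 0.616 |
| 10% | 0.9 | 0.5 | 3.6 v 2.0 | 1.8 | 0.685 |
| 10% | 0.9 | 0.3 | 3.6 v 1.2 | 3.0 | 0.820 |
| 5% | 0.9 | 0.9 | 1.8 v 1.8 | 1.0 | 0.39 |
| 5% | 0.9 | 0.7 | 1.8 v 1.4 | 1.3 | 0.47 |
| 2% | 0.9 | 0.9 | 0.72 v 0.72 | 1.0 | 0.31 |
| 2% | 0.9 | 0.5 | 0.72 v 0.40 | 1.8 | 0.39 |

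Worked line: 40 × 0.10 × 0.9 = 3.6 and 40 × 0.10 × 0.3 = 1.2, so the ratio is 3.6/1.2 = 3.0. In that scenario routine care logs nobody with probability (1 − 0.03)^40 = 0.30, against (1 − 0.09)^40 = 0.02 in the intervention arm.

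**5. After the fix.** If events are sought in the same way in both arms, *d* should be about equal. With equal *d* the apparent ratio is 1.0 at every assumed risk.

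**The case against.** The case on the other side is substantial, and most of it limits how far the point can go.

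- **How events are found.** A reader might infer that events are logged only if someone volunteers them. The text does not say so. The 24-hour rule is a deadline for sending the form and does not exclude active enquiry.
- **Unseen documents.** A safety protocol is announced, and the Routine care section shows that it holds content the Safety section does not set out (collecting GP contact details). A journal article may leave the method and schedule of enquiry to such a document, so the silence here is not a fault in itself. This does not rescue the definition, which the article states and states too narrowly.
- **Comparability.** A reader might infer that counts by arm are bound to be non-comparable. No adverse event comparison by arm is planned, the Quantitative analysis section disclaims formal testing between groups, and the stated success criteria (recruiting more than 50% of eligible participants, mean attendance above 50%) use no harm count. The risk arises only if counts are shown by arm.
- **Other data.** It would be too strong to say that harms outside the definition are never captured. Both arms complete the same symptom scales under masked assessment, and treatment received is recorded for all. This softens the problem but does not remove it: the BSS covers thoughts and not attempts, and none of these sources feeds the form.
- **Weekly committee review.** It adds oversight, but it is not participant contact, and the committee can review only what reaches it.
- **Magnitude.** The detection rates are assumed. At 5% risk with 90% against 70% detection, the chance of an apparent excess rises only from 0.39 to 0.47.

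**Conclusion.** The definition is too narrow as written. This rests on the text alone and needs no assumption: harms other than the two named events trigger no form.

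Unequal detection is a conditional risk. It follows from the contact schedule the article describes, and it matters if adverse event counts are shown by arm without a common enquiry behind them. Its size cannot be fixed from the article. With equal true risk and 90% detection in the intervention arm, the apparent ratio runs from 1.3 (70% detection in routine care) to 3.0 (30%). At the low event numbers likely with 40 per arm, chance also plays a large part.

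The documents do not support the stronger conclusion that suicide attempts and self-harm will be under-counted or that the arms cannot be compared. The change is still worth making, because it is cheap and closes a stated gap in safety capture.

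**What to change.** 1. In the Safety section, replace *i.e.* with *including*, and define an adverse event generally as any untoward medical or psychological event, with deaths and hospital admissions listed alongside suicide attempt and self-harm.
2. Reconcile this wording with the announced safety protocol, so that the two give one definition.
3. Put one identical adverse event question set to both arms at the existing week-16 assessment.
4. Take any counts shown by arm from that common enquiry, and list events volunteered in therapy sessions separately.

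No visit is added and treatment is unchanged. The cost is a wording change, a few more minutes at one assessment, and more forms to process.

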## Discussion

The proposed study will provide evidence on feasibility and acceptability of a culturally adapted manually assisted psychological intervention for individuals who screen positive on measures of eating disorders. The findings of the study will provide an opportunity to plan and design a fully powered randomized controlled trial to evaluate clinical and cost-effectiveness of Ca-GBBB. Both the quantitative, and qualitative results of this feasibility study may contribute to improve clinicians and researchers’ understanding on what is likely to be effective for individuals with eating disorders. In LMICs, particularly Pakistan, there remains a substantial deficit in evidence on management of EDs, and this study will be the first trial evaluating the feasibility of the culturally appropriate psychological intervention for this population.

The study will produce the following outputs.A user-friendly, culturally adapted, Urdu translated manual of Ca-GBBB.A training tool kit for students, researchers, academics and clinicians.Simple awareness leaflets in national and regional languages.Publications in peer reviewed, open access journals.Lay summaries of findings ready to be disseminated through different platforms including social media.A dissemination plan for the study will be prepared in collaboration with the CEI group. The findings will be presented in local, national and international conferences.

## Data Availability

The anonymized data will be available upon request by email to the corresponding author.

## Appendix 1: Topic Guide-Participants

**Instruction to interviewer:** The following interview schedule serves as a guide. Whilst the interviewer should endeavour to cover the content of the interview schedule, precise wordings and questions may be varied as required.

**Instructions to participant:**

We are meeting today to ask you about your experience of participating in the intervention programme, including your thoughts about any barriers or challenges that you may encountered during participation. This interview will help us to improve this intervention programme.

**Introduction, setting ground rules:**

Introduce yourself, thank participant for taking part and confirm agrees to interview taking place.

Ensure environment is comfortable.

Discuss the following issues:

- Review the nature and purpose of the research.
- No right or wrong answers, aim to understand experiences/views.
- Confidentiality, use of data.
- Explain the use of data recorder, transcription, use of pseudonym (invite to choose), use of verbatim quotes, will be taking field notes.
- Researcher should understand that  discussion might bring up difficult memories, explain that the participant can decline to answer any question or prompt; they can ask to stop at any time if feels need to.
- Expected duration of interview.
- Check consent form signed.
- Ask if any questions.

Check recorder working.

Introduce and switch on tape recorder.

General prompts.

- Allow participant to respond uninterrupted and use open prompts if required to explore aspects of their experiences in depth.
- Can you tell me more about XXX?', 'What makes you say XXX?, How did XX make you feel?

## Start of interview

I’m going to ask you first about your experience of the training/intervention program.

1: Could you please share your experience of participating in sessions? How was it like for you?

**Prompts:**

- What did you expect from this sessions/intervention? Was the program able to meet your expectations? if yes, can you please explain? if No, can you please talk more about this?
- What was helpful? and why?
- What was not very helpful? and why?
- Easy or difficult to understand?
- How was it getting to the sessions? (e.g. remembering, transport, time)

2: Can you share your experience about the topics you discussed during your meetings with therapists?

**Prompts**

- Psychoeducation about Eating Disorders
- Making your decision: Setting the goal
- Psychoeducation regarding body shape
- Health Hazards of dieting
- Letter for Hope
- Learning to Detect Early Symptoms of Relapse
- Understanding behavioural chain: ABC Model
- How to stop binges
- Childhood Wounds
- Putting assertiveness into practice
- Working to live, living to work

3: Did the trainer/therapist ask you to do anything in sessions (activities)? What was this like?

